### Analysis plan

#### Primary endpoints—SMC, IPTp-SP, and ANC analysis

The primary outcome will be the individual level binary indicator for presence or absence of at least three doses of IPTp-SP in women included in the endline IPTp-SP HHS, and the intervention effect will be estimated using a generalized linear mixed model with a logit link function and a random intercept term for cluster – period, expressed as odds ratio and 95% confidence intervals. The primary analysis will be done by country. In a secondary analysis, data of both countries will be combined using an individual patient data meta-analysis approach to assess the overall efficacy of the intervention.

Evolution over time, and by arm, of the use of ANC (number and timing of contacts) will be assessed using routine data and modelling-temporal analysis. In addition, a multilevel logistic regression model will be performed to identify individual and contextual factors associated with ANC attendance and IPTp-SP coverage at baseline. Multilevel modelling will be selected due to the clustering of the collected data.

Differences in SMC coverage (3 or 4 doses) and ANC uptake (4 visits) between control and intervention arms at endline will be assessed using multilevel regression models.

No interim analysis will be conducted.

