#### Sampling methods

Four household surveys (HHS) will be carried out. Two at baseline, one to assess participants’ baseline characteristics, IPTp-SP coverage, and ANC attendance rate, and one for SMC coverage. Two at endline, one to measure the primary endpoint (i.e., IPTp3 + coverage) and one to measure SMC coverage. In each country, a multi-stage cluster sampling method will be followed to select the clusters (health facility and its catchment area) from the study sites that will be included in the HHS. The sampling will be carried out in three stages in each study site (Fig. 2), namely: (1) random selection of ‘clusters’ using probability proportional to size (PPS); (2) random selection of households in each ‘cluster’ using maps and household listing. Mapping and listing of the households will be completed before the baseline IPTp-SP or SMC HHS begins. These households will be selected by equal probability; (3) simple random selection of the woman or guardians of SMC children to be interviewed in each household among those meeting the inclusion criteria. A single child will be selected per HH to minimize the cluster effect. When several eligible women are present in a household, the woman with the most recent birth will be chosen.

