### Sample size calculation

#### Primary endpoint – IPTp3 + at endline

The primary endpoint will be collected at endline among women with a child less than 12 months.. It will be the individual level binary indicator for presence or absence of at least three doses of IPTp-SP through ANC alone or ANC plus SMC delivery platforms. Since baseline prevalence of IPTp-SP coverage highly differs between Mali and Burkina Faso, the sample size was calculated for each country separately.

In Mali, with 10 clusters per arm, 48 women sampled per cluster will be required at endline to detect a 45% increase in the relative risk of women receiving at least 3 doses of IPTp-SP between control and intervention arms, with 80% power, alpha = 5%, an intra-cluster correlation coefficient (ICC) of 2.5% and 5% primary endpoint missing rate, assuming this proportion to be 28% in the control arm [20]. Based on this assumption a total of 1,008 women will be included (Shiny CRT calculator®) [21]. With this sample size, we should be able to demonstrate a 33% in the relative risk of women receiving at least 3 doses of IPTp-SP assuming this proportion to be 40% in the control arm as recently reported in an HHS conducted in a neighboring area, Bankass in Mopti region ([name] et al., 2022, unpublished data). Assuming that there will be at least one eligible woman in every 5 households, a total of 5,040 households will be visited.

In Burkina Faso, with 10 clusters per arm, 46 women sampled per cluster will be required at endline to detect an increase of 22% in the relative risk of women with at least 3 doses of IPTp-SP between the control and intervention arms, with 80% power, alpha = 5%, an ICC of 2.5% and 5% primary endpoint missing rate, assuming this proportion to be 58% in the control arm [18]. Based on this assumption a total of 966 women will be included. Assuming that there will be at least one eligible woman in every 5 households, a total of 4,830 households will be visited.

A possible adjustment of the number of women to be interviewed in the endline surveys will be made based on the baseline data: IPT3 + coverage; proportion of non-response and calculated ICC.

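### The primary model names no baseline term, and its cluster–period random intercept gives the already collected baseline IPTp3+ coverage no role on either reading: an efficiency gap, not an error

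*Protocol article*

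**What the plan says.** The analysis plan (Primary endpoints—SMC, IPTp-SP, and ANC analysis) defines the primary outcome as a "binary indicator for presence or absence of at least three doses of IPTp-SP in women included in the endline IPTp-SP HHS". The effect comes from a "generalized linear mixed model with a logit link function and a random intercept term for cluster – period", reported as an odds ratio. The level of analysis is also fixed: "The primary analysis will be done by country". No covariate, arm-by-period term or other use of baseline data is named for this model.

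The same outcome is measured before the intervention. Under Sampling methods, one baseline household survey covers "baseline characteristics, IPTp-SP coverage, and ANC attendance rate". Table 1 plans 775 women in Mali and 786 in Burkina Faso, and Table 2 lists the primary outcome at both baseline and endline. Three uses of the baseline survey are stated: estimating coverage, possibly re-sizing the endline survey, and a separate multilevel model of factors associated with coverage at baseline. None of them serves the comparison between arms.

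The randomisation section describes 1:1 allocation of facilities and mentions no stratification or balancing on coverage.

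**The concern.** A cluster–period intercept differs from a cluster intercept only when more than one period is modelled, yet the outcome sentence restricts the data to endline women. There are two ways to read this.

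- **Endline data only.** There is one period, so the term is just a cluster intercept and the baseline survey is unused.
- **Both surveys.** A cluster–period intercept with no cluster intercept makes the baseline and endline effects of the same facility independent. Facilities that start high are then not expected to stay high, and baseline cannot adjust the endline comparison at cluster level.

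Each country is analysed on 20 clusters, so chance differences between arms in facility coverage can matter. At the plan's ICC of 0.025, the arm difference in true cluster coverage arising by chance has SD √(2 × 0.025 × p(1−p)/10). That is √(0.05 × 0.2016/10) = 3.2 points in Mali (p = 0.28) and √(0.05 × 0.2436/10) = 3.5 points in Burkina Faso (p = 0.58). The target differences are 12.6 and 12.8 points. Baseline coverage could absorb part of this variation. If the wording is settled only after endline data are seen, the choice of model also becomes discretionary.

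**Working it through.** **Inputs from the sample size section.** Mali: "with 10 clusters per arm, 48 women sampled per cluster will be required at endline to detect a 45% increase in the relative risk", control proportion 28%. Burkina Faso: "with 10 clusters per arm, 46 women sampled per cluster will be required at endline to detect an increase of 22" per cent in relative risk, control proportion 58%. Both: "with 80% power, alpha = 5%, an intra-cluster correlation coefficient (ICC) of 2.5% and 5% primary endpoint missing rate". Two-sided testing is assumed, since the protocol does not state sidedness.

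**Step 1: reproduce the plan's figure.** Variance of the difference = [p1(1−p1) + p2(1−p2)] × [1 + (m−1) × ICC] / (10m); power = Φ(d/SE − 1.96).

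- Mali: p2 = 0.28 × 1.45 = 0.406, d = 0.126. Design effect = 1 + 47 × 0.025 = 2.175. Variance = 0.4428 × 2.175/480 = 0.002006, SE = 0.0448, d/SE = 2.813, power 80.3%. Total = 48 × 20 × 1.05 = 1,008, as stated.
- Burkina Faso: p2 = 0.58 × 1.22 = 0.7076, d = 0.1276. Design effect = 1 + 45 × 0.025 = 2.125. Variance = 0.4505 × 2.125/460 = 0.002081, SE = 0.0456, d/SE = 2.797, power 79.9%. Total = 46 × 20 × 1.05 = 966, as stated.

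The stated sizes therefore rest on a plain endline comparison with a normal reference. With a t reference on 18 df, the same design has power 75.8% in Mali and 75.3% in Burkina Faso.

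**Step 2: what baseline adjustment could add.** Adjusting cluster results for baseline cluster coverage multiplies the variance by (1 − r²), where r² = CAC² × R0 × R1 and R = m × ICC/[1 + (m−1) × ICC]. CAC is the correlation of true cluster coverage between baseline and endline. The documents give no value, so it is varied. Assuming all 20 clusters are surveyed at baseline, m0 = 775/20 = 38.75 (Mali) and 786/20 = 39.3 (Burkina Faso).

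- Mali: R1 = 0.552, R0 = 0.498, product 0.275.
- Burkina Faso: R1 = 0.541, R0 = 0.502, product 0.272.

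**Step 3: charge the cost of adjustment.** One degree of freedom is lost (17 df). Estimating the slope from 20 clusters inflates the variance by about 1 + 1/16. The net variance factor is (1 − r²) × 17/16. For Mali at CAC 0.8, r² = 0.64 × 0.275 = 0.176, the factor is 0.824 × 1.0625 = 0.876, the noncentrality is 2.813/√0.876 = 3.006, and power on t(17) is 80.9%.

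| Assumed CAC | r² Mali | Power Mali | r² Burkina Faso | Power Burkina Faso |
|---|---|---|---|---|
| unadjusted, 18 df | – | 75.8% | – | 75.3% |
| 0 | 0 | 73.0% | 0 | 72.5% |
| 0.5 | 0.069 | 76.0% | 0.068 | 75.5% |
| 0.7 | 0.135 | 79.0% | 0.133 | 78.4% |
| 0.8 | 0.176 | 80.9% | 0.174 | 80.3% |
| 0.9 | 0.223 | 83.1% | 0.220 | 82.5% |

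Break-even is at a CAC of about 0.5 in both countries. Leaving out the slope cost would add about 2 to 2.5 points to each adjusted figure and make the gain look larger than it is.

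**The case against.** The strongest reply is that nothing here is wrong. An unadjusted endline comparison of randomised clusters is valid, it is the basis on which the sample size was built, and the choice of covariates is often left to an analysis plan, which is not shown. The first two parts stand in full. The third stands in part: the article may leave covariates open, but it does fix the population, link, random effect and level of analysis, and the random effect it fixes does not fit the stated data.

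Four stronger readings are tempting, and the documents do not support them.

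- *The analysis is biased.* Chance imbalance under randomisation costs precision; it does not bias the estimator.
- *Baseline is definitely excluded.* The outcome sentence points to endline only, but the cluster–period term and the listing of the outcome at both times in Table 2 point the other way. The text does not settle it.
- *Baseline is measured in the same clusters.* Survey clusters are drawn with probability proportional to size, and the number drawn at baseline is not given. Endline needs 10 per arm in each country, which is all 40 facilities, so any trial facility surveyed at baseline recurs at endline. Complete baseline coverage remains an assumption.
- *The precision is free.* The gain depends on an undocumented correlation. The two-year intervention period, and the study's supply of SP to both arms to prevent stock-outs, could weaken it.

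The planned baseline numbers also include a 5% non-response allowance, so analysable women would be about 37 per cluster. That lowers the adjusted figures by at most about 0.3 points.

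**Conclusion.** The point holds as one of efficiency and clarity. The stated random-effects structure gives the baseline survey no part in the primary comparison on either reading, and the sentence should say which data enter.

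At the plan's ICC of 0.025, prespecified adjustment would be worth about 3 to 7 points of power per country if the between-period correlation is 0.7 to 0.9. It is worth essentially nothing at 0.5 and loses about 3 points near 0. It brings power back to about 80% under t-based inference only at a correlation of about 0.8 or more, so it should not be presented as certain to restore the planned power.

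These figures assume two-sided 5% tests, equal cluster sizes, all 20 clusters per country surveyed at baseline, and a cluster-level approximation to the logit model. The correlation is an assumption throughout. A reader might infer that the primary result would be invalid without adjustment; the documents do not support that.

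**What to change.** Before endline data are seen, state whether baseline data enter the primary model and correct the random-effects term to match. Then prespecify, for each country, one of the following:

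1. The endline logit mixed model with a cluster random intercept and the cluster's baseline IPTp3+ coverage (log-odds) as covariate. This needs every randomised cluster to have been surveyed at baseline.
2. A model of both surveys with a common baseline mean across arms (constrained baseline) and random effects for both cluster and cluster–period. This also tolerates clusters without baseline data.

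Keep the unadjusted endline model as a sensitivity analysis. State how many clusters were surveyed at baseline, since that decides whether the first option is available.

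The cost is a change of wording, one degree of freedom for the covariate, and the risk of a small loss of power if facility coverage turns out to be poorly correlated over time. No new data collection is needed if all clusters were surveyed at baseline.

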#### Feasibility and acceptability data analysis

Qualitative data analysis will use a standard thematic procedure. The transcripts will be read and coded by the researchers using the topic guide and the initial coding frame. Conceptual maps will be used to explore relationships and connections in the data and develop specific questions to investigate in further analysis. We will draw on more than one framework. The acceptability theory will draw on Sekhon’s constructs of acceptability [26]. ‘Intervention, actor, context, mechanism and outcome’ configuration [27] will be developed for individual cases and qualitative comparative analysis aiming to identify drivers of acceptability across cases within and across countries. Framework analysis will be used to identify factors influencing the effectiveness of delivery and scalability of each of the interventions using existing frameworks such as the consolidated framework for implementation research [28] and the building blocks of the health system as defined by the WHO [29].

#### Systems effectiveness

Four systems effectiveness analyses will be undertaken: (1) cumulative systems effectiveness of IPTp-SP delivery on the day of the interview i.e., the proportion of women reporting to have received a dose of 3 tablets of SP in the second trimester; (2) effectiveness of each intermediate process in systems effectiveness of IPTp-SP delivery on the day of the visit; (3) effectiveness of IPTp-SP delivery during the woman’s pregnancy i.e., the proportion of women reporting having completed three or more ANC visits and having received three or more doses of SP at four weeks intervals with the first dose given in the second trimester; (4) effectiveness of IPTp-SP in the community i.e., proportion of women having received SP doses in the community within at least four weeks apart from any other doses received from any source. Potential predictors of systems effectiveness will be assessed using univariate and multivariate adjusted logistic regression analyses.

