#### Sample size – IPTp-SP and SMC coverages at baseline

The baseline HHS will determine IPTp-SP coverage among women who have delivered in the previous 12 months, and SMC coverage among children living in the study districts, in the two countries.

Table 1 shows the sample size calculated for the baseline IPTp-SP and the SMC HHS based on the following equation [22]:

**Table 1 Tab1:** Estimated sample size for baseline IPTp-SP and SMC HHS

Country	Outcomes		Estimated sample size	Estimated number of households to be visited^a^
**Mali**	Estimated IPTp3 +	28%, up to 40%	775	3,875
	Estimated SMC coverage 4 doses	54%	802	802
**Burkina Faso**	Estimated IPTp3 +	58%	786	3,930
	Estimated SMC coverage 4 doses	90%	290	290

^a^It is assumed that at least one woman in every five households will meet the inclusion criteria and there will be a non-response rate of 5%. Sources: MIS 2018, for Burkina Faso [18]; ACCESS SMC partnership [23]; Diawara et al. 2017 [24] and [name] et al. 2022, unpublished data, for Mali

$$n=\frac{DE\cdot{1.96}^2\cdot p\cdot\left(1-p\right)}{{precision}^2}$$

Where Design Effect (DE) = 2, *p* = expected IPTp3 + coverage, or the expected SMC coverage, prevalence precision =  ± 0.05 with a 95% CI. It is assumed that at least one woman in every five households, and one child in every household will meet the inclusion criteria and there will be a non-response rate of 5%.

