#### Secondary endpoints

Feasibility and acceptability

To assess the acceptability and feasibility of IPTp-SP delivery through the ANC + SMC strategy, a purposive sample of 40 to 80 pregnant women of different gravidities and women with a child < 12 months. per country (80 to 160 total) will be recruited at endline. An additional purposive sample of 48 to 72 women will be selected for Focus Group Discussions (FGDs). Two to four health providers purposively selected from each of the 10 intervention HFs in each country (40 to 80 total) and all consenting CHWs who were involved in the IPTp-SP community delivery will be included. The interviews will also include the DHMTs and Ministry of Health staff in the National Malaria Control and Reproductive Health departments (approx. 5 per site, *n* = 10).Systems effectiveness

ANC exit interviews will be conducted with pregnant women when leaving the HF at endline to assess the systems effectiveness of the IPTp-SP delivery in both arms (intervention and control). In Mali, a sample size of 699 women from 20 HF will allow the detection of an estimated 35% of women achieving the primary endpoint of IPTp3 + with a precision of ± 5%, 95% CI, and a DE of 2. In Burkina Faso, a sample size of 699 women from 20 HF will allow the detection of an estimated 65% of women achieving the primary endpoint of IPTp3 + with a precision of ± 5%, 95% CI, and a DE of 2.Exploratory COVID

To assess women’s ANC and IPTp-SP care seeking practices and any impact that the COVID-19 pandemic had on delivery and access at baseline, a purposive sample of 8–12 pregnant women of different gravidities and women with a child < 12 months. will be selected (80–120 women per country for a total of 160–240) for FGD, and a purposive sample of 2–3 health care providers will be selected from 10 HFs in both countries (20–30 per country for a total of 40–60) for in-depth interviews.

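### The exit-interview measure of three visits and three doses is taken in women still pregnant, sized as if it were the post-delivery primary endpoint, and precise to about ±7 points per arm

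*Protocol article*

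**What the plan says.** All references are to the protocol article.

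- **Analysis plan, Systems effectiveness.** Four analyses are listed. The third, effectiveness during the woman's pregnancy, is "the proportion of women reporting having completed three or more ANC visits and having received three or more doses of SP at four weeks intervals". A further condition is that dosing begins in the second trimester. No minimum gestational age or visit number is given for the denominator.
- **Data collection, Secondary endpoints.** The respondents are pregnant women approached on arrival at the facility and interviewed as they leave ANC. The questionnaire covers current pregnancy history and earlier doses from ANC or from home visits.
- **Sample size calculation, Secondary endpoints.** The interviews are meant "to assess the systems effectiveness of the IPTp-SP delivery in both arms (intervention and control"). The Mali figure is justified thus: "a sample size of 699 women from 20 HF will allow the detection of an estimated 35% of women achieving the primary endpoint". The endpoint meant is IPTp3+, and the target is ±5 points at 95% confidence under a design effect of 2. Burkina Faso has the same 699 women with 65%.
- **Sample size calculation, Primary endpoint.** That endpoint is collected from women with a child under 12 months and counts "at least three doses of IPTp-SP through ANC alone or ANC plus SMC delivery platforms". Each country has 10 clusters per arm.
- **Randomization and treatment allocation.** Control-arm women get their doses only at scheduled ANC visits. Intervention-arm women can also get them in the SMC rounds.

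**The concern.** One label is used for two different quantities. The household survey looks back over completed pregnancies. The exit interview catches women part-way through, some at a first or second visit. A woman at her second visit cannot meet a three-visit criterion, and three doses four weeks apart take at least 2 × 4 = 8 weeks from the first dose. Such women count as failures only because of when they were interviewed.

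The success rule also differs from the primary endpoint. It adds three ANC visits to the three doses, in a trial whose intervention delivers doses outside ANC. Finally, the survey is meant to describe both arms, yet the sample size is worked out for the country as a whole.

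Assessing systems effectiveness is listed as primary objective (3), and the abstract names exit interviews beside household surveys as the means of assessing IPTp3+ effectiveness. Readers would be given two IPTp3+ figures per arm that look comparable and are not, with a precision that does not apply to either arm.

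**Working it through.** **1. Reproduce the 699.** The baseline-survey section gives n = DE × 1.96² × p(1−p) / precision². With DE = 2, precision 0.05 and p = 0.35 or 0.65, p(1−p) = 0.2275 in both cases:

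n = 2 × 3.8416 × 0.2275 / 0.0025 = 699.2.

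The plan's figure is reproduced, for all 20 facilities, so for both arms together.

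**2. Precision per arm.** Half of 699 is 349.5. Half-width = 1.96 × √(DE × p(1−p) / 349.5).

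| Assumed proportion | Half-width per arm |
|---|---|
| 35% or 65% | ±7.07 points |
| Mali control, 28% | ±6.7 |
| Mali intervention, 28% × 1.45 = 40.6% | ±7.3 |
| Burkina Faso control, 58% | ±7.3 |
| Burkina Faso intervention, 58% × 1.22 = 70.8% | ±6.7 |

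The half-width of the between-arm difference is about ±9.9 points in Mali and ±10.0 in Burkina Faso. For ±5 points in each arm, about 2 × 699 = 1,398 women per country would be needed. If the design effect is instead built from the primary endpoint's ICC of 2.5% with 34.95 women per facility, DE = 1 + 33.95 × 0.025 = 1.85 and the per-arm figure is ±6.8, so the result hardly changes.

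**3. Where 35% and 65% may come from.** The article gives no source. The arm averages implied by the primary sample size are (28 + 40.6)/2 = 34.3% and (58 + 70.8)/2 = 64.4%. They fit, which suggests completed-pregnancy rates averaged over arms. This is an inference.

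**4. How far the exit proportion can move.** Illustration by assumption: a fraction p of women end with three or more doses after v visits, one dose per visit; the rest make two visits; every visit is equally likely to be sampled. The share of exit interviews that count as successes is p(v−2) / [pv + 2(1−p)].

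| v | p = 35% | p = 65% |
|---|---|---|
| 3 | 0.35/2.35 = 14.9% | 0.65/2.65 = 24.5% |
| 4 | 0.70/2.70 = 25.9% | 1.30/3.30 = 39.4% |
| 5 | 1.05/3.05 = 34.4% | 1.95/3.95 = 49.4% |
| 6 | 1.40/3.40 = 41.2% | 2.60/4.60 = 56.5% |
| 8 | 2.10/4.10 = 51.2% | 3.90/5.90 = 66.1% |

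Two forces compete. Interviewing before the end of pregnancy lowers the proportion, and over-sampling of frequent attenders raises it. The same completed-pregnancy rate can produce very different exit figures, above or below it.

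**5. The visit condition by arm.** In the control arm every dose comes from an ANC visit and doses are monthly, so three doses nearly imply three visits and the condition adds little. In the intervention arm a woman with two ANC visits and a further dose from an SMC round has three doses but fails.

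**6. Effect of restricting the denominator.** If half the women are eligible by gestational age (assumption), 174.75 per arm remain: 1.96 × √(0.455/174.75) = ±10.0 points at 35% or 65%.

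**The case against.** Much can fairly be said for the plan. The ±5 points is right for the country sample and is never claimed for each arm; the plan names no between-arm test for these analyses, and its predictor regressions can use everyone. Only analysis (3) is affected: (1) and (2) concern the day of the visit, and (4) deals with community doses. The any-platform comparison rests on the household survey, which is untouched. A composite of attendance and dosing is a legitimate thing to measure in an ANC survey. A gestational-age window could sit in an analysis plan that is not shown. And if the true exit proportion is low, the half-width shrinks, to ±5.3 points per arm at 15% or ±5.9 at 20%.

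These points limit the concern but do not remove it. The article itself equates the exit proportion with an endpoint it defines in another population, whatever a later document adds. Analysis (4) concerns the spacing of community doses from others, not three or more doses from any source, so it does not replace the missing figure. The ±7 points is the per-arm counterpart at the plan's own assumed rates and should be labelled so.

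A reader might infer that systems effectiveness is generally biased low, or that the intervention arm is penalised. The documents support neither. Step 4 gives values above as well as below the completed-pregnancy rate. The visit condition works against the intervention arm, but monthly community rounds could bring women to three doses sooner, and the strategy aims to raise ANC attendance. The article hypothesises more attendance, not explicitly earlier attendance, so an argument from earlier first visits has no footing.

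**Conclusion.** The point holds for analysis (3) only. As written, its proportion depends on the gestational-age and visit mix at ANC exit, should not be set beside household-survey IPTp3+, and carries a visit condition that acts unequally on the arms. Neither the direction of any error nor the net effect on the arm comparison can be fixed from the documents. Per-arm precision is about ±7.1 points at 35% or 65% (±6.7 to ±7.3 at the arm-specific rates), against ±5 pooled. This assumes an equal split of the 699 women, DE 2 and the plan's assumed rates. The primary analysis is not affected.

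**What to change.** 1. In analysis (3), restrict the denominator to women whose gestational age at interview allows three doses at the plan's own four-week interval, or report doses received over doses possible by that age.
2. Report three or more doses from any platform, by arm, and show the three-visit criterion separately.
3. In the exit-interview sample size, say that ±5 points is for both arms pooled, give about ±7 points per arm at the assumed rates, and note that this widens once the denominator is restricted (about ±10 if half are eligible).
4. Stop labelling the exit-interview proportion as the primary endpoint.

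These are changes of wording and analysis. The pregnancy history and prior-dose items, including home-visit doses, are already in the questionnaire. The cost is a smaller denominator for analysis (3) and a less favourable stated precision.

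### The regression for predictors of systems effectiveness makes no allowance for facility clustering, although the same survey is sized for it and a parallel analysis in the plan models it

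*Protocol article*

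**What the plan says.** All references are to the protocol article.

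- **Analysis plan, Systems effectiveness.** After listing four analyses based on proportions and process steps, it adds: "Potential predictors of systems effectiveness will be assessed using univariate and multivariate adjusted logistic regression analyses". It lists no predictors and does not say how variances will be estimated.
- **Sample size calculation, Secondary endpoints.** The exit interviews cover both arms. For Mali: "In Mali, a sample size of 699 women from 20 HF will allow the detection of an estimated 35% of women achieving the primary endpoint". For Burkina Faso: "In Burkina Faso, a sample size of 699 women from 20 HF will allow the detection of an estimated 65% of women". Both figures are set "with a precision of ± 5%, 95% CI, and a DE of 2".
- **Analysis plan, Primary endpoints—SMC, IPTp-SP, and ANC analysis.** For a comparable search for associated factors in the baseline survey, "a multilevel logistic regression model will be performed to identify individual and contextual factors associated with ANC attendance and IPTp-SP coverage at baseline". The reason follows: "Multilevel modelling will be selected due to the clustering of the collected data". The same section uses multilevel models for endline SMC and ANC uptake, and a mixed model with a cluster-period random intercept for the primary outcome.

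**The concern.** Women interviewed at the same facility share providers, local practice and trial arm, so their outcomes are correlated. The plan accepts this when it sizes the exit survey: without the design effect, half as many women would do. The sentence naming the regression then drops the facility, whereas the other regressions on individual survey data in the plan name a multilevel or mixed model.

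A logistic model with no clustering term treats the 699 women per country as independent. For a predictor that takes one value per facility, the information comes mainly from 20 facilities rather than 699 women. Intervals would be too narrow, and facility-level or strongly facility-clustered factors would be declared predictors too often. Systems effectiveness is listed as a primary objective, although its sample size and data collection appear under Secondary endpoints.

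**Working it through.** **Inputs**

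- 699 women, 20 facilities, expected proportions 35% (Mali) and 65% (Burkina Faso), half-width 0.05, design effect (DE) 2: Sample size calculation, Secondary endpoints.
- Formula n = DE × 1.96² × p(1 − p) / d²: given for the baseline surveys, where "Where Design Effect (DE) = 2, *p* = expected IPTp3 + coverage, or the expected SMC coverage, prevalence precision = ± 0.05 with a 95% CI".
- The trial's planning ICC, as a sensitivity value: "an ICC of 2.5% and 5% primary endpoint missing rate" (Primary endpoint – IPTp3 + at endline).

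**Step 1. Reproduce the plan's figure.** 2 × 1.96² × 0.35 × 0.65 / 0.05² = 699.17, and the same at 0.65 × 0.35. This matches 699. With DE = 1 the result is 349.6. Half the sample is therefore there to pay for clustering.

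**Step 2. Implied ICC.** Mean cluster size m = 699 / 20 = 34.95. ICC = (DE − 1)/(m − 1) = 1 / 33.95 = 0.0295, close to the 2.5% used for the primary endpoint.

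**Step 3. Facility-level predictor.** The naive standard error is too small by √DE. The actual size of a nominal two-sided 5% test is 2[1 − Φ(1.96/√DE)].

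| Assumption | DE | √DE | Type I error | Coverage of a 95% CI | Effective n |
|---|---|---|---|---|---|
| Plan's DE | 2 | 1.41 | 16.6% | 83.4% | 349.5 |
| ICC 2.5%: 1 + 33.95 × 0.025 | 1.85 | 1.36 | 14.9% | 85.1% | 378 |

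**Step 4. Predictors that vary within facilities.** The usual approximation for one coefficient is 1 + (m − 1) × ICC(outcome) × ICC(predictor). At the implied outcome ICC, (m − 1) × ICC(outcome) = 1, so this becomes 1 + ICC(predictor). The documents give no predictor ICCs; the values below are assumptions chosen to show the range.

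A simulation checks the approximation: 20 facilities of 35 women, beta-binomial outcome with mean 35% and ICC 0.0295, logistic regression with no clustering term, Wald test, 3,000 runs. Its Monte Carlo standard error is √(0.05 × 0.95 / 3,000) = 0.4 percentage points at 5%, and √(0.167 × 0.833 / 3,000) = 0.7 at 16.7%.

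| Predictor ICC (assumed) | Approximate DE | Type I error, formula | Type I error, simulated |
|---|---|---|---|
| 1 (constant within facility) | 2 | 16.6% | 16.7% |
| 0.5 | 1.5 | 11.0% | 11.3% |
| 0.1 | 1.1 | 6.2% | 6.0% |
| 0 | 1 | 5.0% | 5.0% |

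Formula and simulation agree. The harm depends on how strongly the predictor itself clusters by facility.

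**The case against.** The strongest reply is that the article is silent here rather than wrong. It never says clustering will be ignored, and logistic regression with a facility effect or robust errors would fit its words. The authors plainly know the data are clustered, and a condensed article may leave the variance method of a supporting analysis to the full document. Part of this stands: one cannot conclude that a naive analysis is intended. But the article does name a model, and for a parallel analysis in the same plan it names the clustered version and gives the reason. That contrast is an inconsistency in the text, not merely an omitted detail.

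Second, no predictors are listed, and the exit questionnaire described under Data collection covers mostly woman- and visit-level items: demographics, pregnancy history, reason for attending, doses received. For many of these the inflation may be small. This stands and limits the point. Arm is an obvious candidate, since both arms are interviewed, but the text does not say it will be in the model.

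Third, the design effect of 2 is a planning value for a proportion and does not carry over to every coefficient. This also stands; it is why the figures are tied to facility-level predictors and shown at a second ICC.

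A reader might also infer that false predictors would shape scale-up recommendations. The documents do not support that: they assign factors bearing on scalability to qualitative framework analysis.

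**Conclusion.** The point holds in a limited form. The stated regression makes no allowance for facility clustering, which is inconsistent with how the same survey was sized and with how the plan treats a similar analysis. Taken literally, standard errors would be too small by a factor of about 1.4 for a predictor fixed within facilities, with type I error of about 15% to 17% at a nominal 5%. This assumes roughly equal facility samples, an outcome ICC between 0.025 and 0.0295, and that such predictors are included. For predictors that vary mainly within facilities the error stays near 5% to 6%.

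A reader might infer that every standard error in this regression is wrong, or that the trial's main conclusion is at risk. Neither follows. Weakly clustered predictors are barely affected, and the primary endpoint has its own mixed model. Nor do the four systems-effectiveness proportions come into question: no interval method is stated for them, and their precision was already planned with the design effect. This is a should-fix.

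**What to change.** In the Systems effectiveness part of the analysis plan, state that predictors will be assessed by logistic regression that accounts for facility, fitted by country, in line with the baseline factor analysis. Choose one of two forms in advance:

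- a facility random intercept; or
- GEE or cluster-robust standard errors with a small-sample correction, because there are only 20 clusters per country and uncorrected robust errors tend to be too small at that number.

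If the full protocol or analysis plan already says this, carrying the phrase into the article is enough. The change needs no new data and no more women, since the sample already includes the design effect. The cost is wider confidence intervals, mainly for facility-level and strongly clustered predictors.
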